### Azithromycin absorption

High-vaginal specimens collected by the research nurse at the day 7 visit will be preserved in 1 ml of 100% methanol and stored at −80°C prior to analysis. Azithromycin levels are thought to remain well above the reported MIC for chlamydia for between 10 to 14 days post-treatment with 1 g dose [30,31]. Azithromycin levels in high-vaginal material (cells and mucus) will be measured using a validated liquid chromatography – tandem mass spectrometry method (LC-MS/MS) [47-50]. An azithromycin standard curve will be prepared in high-vaginal specimens from a separate individual not exposed to azithromycin, and azithromycin concentrations detected by LC-MS/MS will be normalised to lipid concentrations [50]. Azithromycin concentrations in high-vaginal specimens will be normalised to membrane lipid concentrations and then calculated using the standard curve.

### Immunological markers

Blood specimens will be taken at the recruitment visit and from all women who return a positive test of cure test. Serum will be analyzed for chlamydia antibodies titres against peptide and protein antigens using previously described methods [51,52].

### Chlamydia test results and management

Women will be treated with 1 gram azithromycin according to site protocol at the time of recruitment. Those who have a positive test of cure by PCR at day 28, 42 or 56 will be asked to return to the clinic for further treatment of doxycycline 100 mg twice daily for ten days. All laboratory assay results will be forwarded to the study centre and entered into the study database.

### Partner notification

At the time of recruitment, the research nurse will explain the importance of treating sexual partners and avoiding sexual contact for 7 days. Multiple strategies to support partner treatment will be explored. Participants will be given a business card that contains the web address for *Let Them Know* (http://www.letthemknow.org.au/), a partner notification service for sexual contacts of chlamydia and other STIs. *Let them know* allows individuals to send a message to a partner, either anonymously or named, by SMS or email. If preferred, women may direct their partners to call the research nurse for information and a referral to appropriate clinical care. Women may also consent to have their sexual partner(s) contacted for a telephone consultation and, if appropriate, prescribed azithromycin treatment for partner or mail delivery. This method has been used in several studies at Melbourne Sexual Health Centre and has been very effective at maximizing partner treatment [53,54].

### Data collection

Participants will be asked to complete questionnaires at the time of recruitment and each week until they reach study endpoint. The following data will be collected:

• Age, height, weight

• Genital symptoms

• Reason for attending clinic for their initial test

• Current medications including contraceptives and concurrent antibiotics

• Date of last menses

• Sexual practice data including number of sexual partners, type of sexual partners (casual, occasional, once off or regular), type of sexual contact (vaginal or anal sex), condom use; and

• Whether partners have been notified and treated

### Data analysis

#### Sample size estimates

To detect a treatment failure risk of 8% with a 95% CI of 5.5%, 10.5%, 450 women are required. If the risk of treatment failure is observed to be 3% (as reported by the earlier meta-analysis [22]), then a sample size of 450 generates a 95% CI of (1.7%, 5.0%). To account for a loss to follow up of 15% based on previous studies [8], 520 women will be recruited.

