### Statistical analysis

The population risk of treatment failure will be estimated as the observed proportion of women in the sample with treatment failure, with 95% CI calculated assuming an underlying binomial distribution. Multinomial logistic regression will be used to explore the association between the three-level outcome variable (treatment failure, treatment success, re-infection) and risk factors such as the impact of organism load, azithromycin absorption and MIC. One advantage of a multinominal model over two separate logistic regression models (one comparing the prevalence of treatment failure with treatment success, the other comparing the prevalence of re-infection with treatment success) is that the question of whether treatment failure and re-infection share common risk factors can be addressed formally by comparing estimated odds ratios generated by the same model. Linear regression analyses will investigate trends in chlamydia organism load over time and explore any associations with symptoms, chlamydia serovar and participant age. Both linear and multinomial regression models will be implemented with fixed and random regression effects to accommodate the longitudinal and repeated measures nature of the data. All analyses will be conducted in Stata 12.0.

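### Recruiting 520 women leaves 442 evaluable at the stated 15% loss, not the required 450, and the two planning intervals do not come from one method

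*Protocol article*

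**What the plan says.** All the planning figures are in the protocol article under Sample size estimates. The main one is a precision target: "To detect a treatment failure risk of 8% with a 95% CI of 5.5%, 10.5%, 450 women are required". For a lower risk of 3%, taken from an earlier meta-analysis, it says "then a sample size of 450 generates a 95% CI of (1.7%, 5.0" per cent. It then turns the required number into a recruitment target: "To account for a loss to follow up of 15% based on previous studies [8], 520 women will be recruited".

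The section gives no formula for the inflation and names no method for either interval. Under Statistical analysis, the failure proportion is to be reported "with 95% CI calculated assuming an underlying binomial distribution", with no statement of which binomial interval is meant.

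**The concern.** The primary aim is to estimate one proportion, so interval width is the entire justification for the sample size. A reader should be able to go from the recruitment target, through the assumed loss, to the evaluable number and its interval. Here 450, 15% and 520 cannot all hold.

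The two intervals also differ in shape. The one for 8% is symmetric (2.5 points on each side). The one for 3% is not: 3.0 − 1.7 = 1.3 points below and 5.0 − 3.0 = 2.0 points above. The Discussion sets a failure risk near 8% against 2–3% from culture-based studies, so the paragraph invites a comparison of the two intervals. That comparison is less clean if the intervals were computed differently.

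**Working it through.** **Inputs**, all from Sample size estimates: failure risk 8% with interval 5.5% to 10.5% (half-width 2.5 points); 450 women; alternative risk 3% with interval 1.7% to 5.0%; loss 15%; recruitment 520.

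**1. Reproducing 450.** With the normal approximation, n = z²p(1 − p)/d² = 1.96² × 0.08 × 0.92 / 0.025² = 452.4. The stated 450 is this figure, rounded down slightly.

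**2. Reproducing 520.** 450 × 1.15 = 517.5, which rounds to 520. Dividing by the retained fraction gives 450/0.85 = 529.4, so 530. The figure 520 therefore fits multiplication and does not fit division. That is an inference, since no formula is given.

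**3. What 520 delivers.** This step does not depend on how 520 was obtained.
- Evaluable at 15% loss: 520 × 0.85 = 442, which is 8 fewer than 450.
- Largest loss that still leaves 450: 1 − 450/520 = 13.5%.
- Recruitment matching 450 at 15% loss: 530, which is 10 more than 520.

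**4. Effect on precision at 8%** (normal approximation, p ± 1.96 √(p(1 − p)/n)).
- n = 450: 8% ± 2.51 points, 5.49% to 10.51%.
- n = 442: 8% ± 2.53 points, 5.47% to 10.53%.

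To one decimal, both are the printed 5.5% to 10.5%.

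**5. Which method gives the stated intervals at n = 450?** At 8%, 450 women give 36 events. At 3% they give 13.5, which is not a whole number, so 13 and 14 are shown as well.

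| Method (95% interval, %) | 36 events | 13 events | 13.5 events | 14 events |
|---|---|---|---|---|
| Stated in the article | 5.5–10.5 | – | 1.7–5.0 | – |
| Normal approximation | 5.49–10.51 | 1.34–4.44 | 1.42–4.58 | 1.51–4.72 |
| Exact (Clopper-Pearson) | 5.67–10.90 | 1.55–4.89 | 1.63–5.03 | 1.71–5.16 |
| Wilson | 5.83–10.88 | 1.70–4.88 | 1.78–5.02 | 1.86–5.15 |

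Only the normal approximation reproduces the interval for 8%, and it does not reproduce the one for 3%. Agresti-Coull, Jeffreys, logit, log, arcsine and mid-P intervals (the last for whole counts only) were also tried. None gives both stated intervals, and none gives exactly 1.7% to 5.0% at n = 450. The stated 3% interval lies close to the exact, Wilson and logit types, but its method cannot be identified. Several of these methods do give 1.7% to 5.0% for 13 events in 442, but the article attributes the interval to 450.

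**6. One method with whole counts at the number actually delivered.** Exact intervals at n = 442:
- 35/442 = 7.9%: 5.58% to 10.84%.
- 13/442 = 2.9%: 1.58% to 4.98%.

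**The case against.** The strongest reply is that nothing of substance changes. This is an estimation study with no power threshold to miss. At 442 women the normal-approximation interval still rounds to the one printed, 450 was itself a rounded figure, and 520 is only 1.9% below 530. All of that stands, and it limits the point to a correction of stated figures.

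It can also be said that an asymmetric interval is a reasonable choice at 3%, where the normal approximation performs poorly. That is fair as a choice of method. It does not explain why the paragraph uses a different, unnamed method for 8%.

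A reader might go further and infer that the planned upper limit of 10.5% is understated against what the analysis will produce, because the exact interval for 36/450 reaches 10.9%. The documents do not support this, for three reasons. First, the Statistical analysis section says only that a binomial distribution is assumed; normal-approximation, Wilson and exact intervals all meet that description. Second, the move to 10.9% appears at n = 450 already, so it comes from the choice of method and not from the missing 8 women. Third, it is largely a shift: the lower limit rises as well, from 5.49% to 5.67%, and the full width grows only from 10.51 − 5.49 = 5.02 to 10.90 − 5.67 = 5.23 points.

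**Conclusion.** The point holds as two small errors in the sample size paragraph.

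- **Recruitment target.** At the article's own 15% loss, 520 recruits give 442 evaluable women, 8 short of the stated requirement. The half-width at 8% grows by 0.02 points (2.51 to 2.53). This rests only on the printed figures and on reading the 15% as a share of those recruited. That the figure came from multiplying by 1.15 is likely but not documented, and the conclusion does not need it.
- **Planning intervals.** The 8% interval is a normal approximation and the 3% interval is not. At the lower limit the difference is 1.4% against 1.7%; at the upper limit it is 4.6% against 5.0%. Which method produced the second interval cannot be determined.

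Neither error threatens the validity of the study or changes its analysis. No conflict between the planning intervals and the planned analysis has been shown.

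**What to change.** Restate the paragraph so that its figures agree:

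- Give 520 recruited and 442 evaluable at 15% loss, or 520 recruited and 450 evaluable at a loss of 13.5%. If the sponsor wishes to keep both 450 and 15%, the matching recruitment figure is 530.
- Compute both planning intervals by one named binomial method, from whole event counts at the evaluable number stated. With exact intervals at n = 442, these are 5.6% to 10.8% for 35 events (7.9%) and 1.6% to 5.0% for 13 events (2.9%).

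Restating costs a few figures in one paragraph, with no extra participants and no change to conduct or analysis. Choosing 530 would cost 10 more recruits for a gain in precision too small to see at one decimal, so restating is the proportionate course.

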### Statistical analysis

The population risk of treatment failure will be estimated as the observed proportion of women in the sample with treatment failure, with 95% CI calculated assuming an underlying binomial distribution. Multinomial logistic regression will be used to explore the association between the three-level outcome variable (treatment failure, treatment success, re-infection) and risk factors such as the impact of organism load, azithromycin absorption and MIC. One advantage of a multinominal model over two separate logistic regression models (one comparing the prevalence of treatment failure with treatment success, the other comparing the prevalence of re-infection with treatment success) is that the question of whether treatment failure and re-infection share common risk factors can be addressed formally by comparing estimated odds ratios generated by the same model. Linear regression analyses will investigate trends in chlamydia organism load over time and explore any associations with symptoms, chlamydia serovar and participant age. Both linear and multinomial regression models will be implemented with fixed and random regression effects to accommodate the longitudinal and repeated measures nature of the data. All analyses will be conducted in Stata 12.0.

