Repeat infections are generally considered to be re-infections through exposure to an infected partner. However, emerging evidence suggests that treatment failure following azithromycin may account for a substantial proportion and this has led to considerable debate in the medical and scientific literature [12-16]. Among female participants in a partner treatment trial who reported no sexual intercourse after treatment, 22 of 289 (8%; 95% CI: 5%, 11%) had persistent infection suggestive of treatment failure at follow up [17]. Similarly, the treatment failure rate in a cohort of adolescent females was 7.9% (95% CI: 4%, 10.1%) [10]. Both of these studies attempted to differentiate between re-infection and treatment failure using sexual behavior questionnaires. Batteiger et al. (2010) included genotyping as a further tool to identify re-infections, but these studies were based on self-report of sexual behavior which may have been unreliable.

The recommended first line treatment for uncomplicated genital chlamydia infection in most developed countries is a 1 gram dose of the macrolide antibiotic, azithromycin [18-20]. Although doxycycline 100 mg twice daily for 7 days is a second line treatment for uncomplicated chlamydia, it is not widely used because there are concerns about compliance given the longer duration of treatment [21]. A meta-analysis of chlamydia treatment reported a 97% cure rate for azithromycin and 98% for doxycycline [22]. Of the 12 trials included in the meta-analysis, 11 used culture or immunoassay rather than the more sensitive nucleic acid amplification tests (NAAT) to determine microbial cure at study end [22]. Given the use of culture rather than NAATs, it is possible that the treatment efficacies in these trials were over-estimated [12,13,23].

Governments throughout the developed world are pushing for increased chlamydia testing and the Australian government has invested in a large chlamydia screening randomized controlled trial [24]. It is imperative, therefore, to rigorously investigate the adequacy of currently recommended treatment for chlamydia. We describe here a cohort study, the Australian Chlamydia Treatment Study (ACTS), that aims to measure the proportion of chlamydia infected women who fail treatment when treated with 1 gram azithromycin using advanced microbiological techniques to differentiate between re-infection and treatment failure.

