### Research aim

The primary aim is to estimate the proportion of women infected with chlamydia who fail treatment with 1 gram azithromycin, the most widely recommended first line treatment for genital chlamydia infection [18-20]. The secondary aim is to determine the role of *C. trachomatis* organism load, azithromycin tissue absorption of azithromycin and antimicrobial resistance in chlamydia treatment failure.

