### Primary outcome

The primary outcome is the proportion of women who are classified as having chlamydia treatment failure following detection of chlamydia on a self-collected high-vaginal specimen using a polymerase chain reaction (PCR – see below) Specimens will be collected for testing on days 28, 42 or 56 after recruitment (referred to as ‘test of cure’ specimens for the purpose of this study) according to the algorithm in Figure 1. This algorithm follows a previously described method [10] with the addition of the detection of Y chromosome DNA and performing high discriminatory chlamydial genotyping. Y chromosome DNA will be used to validate sexual behaviour data because it can be detected in the vagina for up to 14 days after unprotected intercourse with a male partner [25,26]. Specimens will be collected from participants every 7 days for Y chromosome detection and genotyping will be undertaken on any chlamydia positive specimens collected on days 28, 42 or 56 after recruitment. Chlamydial genotype fingerprinting will be performed to determine any differences in chlamydia strain/serovar between a participant’s baseline specimen and any repeat positive specimens detected at day 28, 42 or 56 [27]. If a woman has the same serovar present at follow up, further testing by multilocus sequence typing (MLST) targeting *ompA* and five house-keeping genes will be undertaken [28,29]. Detection of same MLST type without detection of Y chromosome DNA or any reports of unprotected sex will be classified as treatment failure. If the woman has a different serovar, it will be classified as a re-infection. A repeat positive chlamydia diagnosis will also be classified as a re-infection if the woman’s repeat specimen has the same MLST type and Y chromosome is detected or she reports unprotected sexual contact.

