### Genotyping & quantification of organism load

Chlamydial fingerprinting will be conducted on specimens that are PCR positive at baseline and at test of cure. We will determine the organism load, identify the chlamydia serovar(s) (genovar) of each infection through a series of quantitative PCR assays to establish whether or not the genotype of the chlamydia detected in those women who have a repeat positive is the same as the type present at baseline [27]. Initial qPCR primers and probes have been designed to predict antigenic differences in major outer membrane protein (MOMP) to determine the serovar as previously described [27,36-38]. The primary chlamydia group-specific multiplex quantitative PCR will target conserved regions of the *ompA* gene specific to all chlamydia serovar groups, including the B group (serovars B, E, D, L1, and L2), C group (serovars A, C, H, I, J, K, and L3) or intermediate group (serovars F and G) serovars. This assay will enable quantification of organism load and will be used to direct serovar-specific PCRs to determine serovars present in the specimen, including possibility of mixed serovars [27,39].

Chlamydia organism load in each specimen will be quantified by comparing the crossing-threshold of each specimen to the crossing-threshold of a standard curve constructed by amplifying different known copy numbers of the *ompA* gene. The beta globin gene, present at one haploid copy per nucleated cells [40], will also be quantified using qPCR to assess specimen adequacy as well as to measure sampling variability between participants and specimens by correlation with the number of eukaryotic cells collected. The quantity of chlamydia will be divided by the number of eukaryotic cells and expressed as the number of organisms present per 100 eukaryotic cells [40].

Specimens from participants where the same serovar has been detected at baseline and follow up will undergo further discriminatory confirmation of relatedness using sequencing of *ompA* gene, as well as five house-keeping genes (*hctB,* CT058, CT144, CT172, and CT682 [*pbpB*]) utilizing a multilocus sequence typing (MLST) approach [28,29,41,42]. This will include the amplification and sequencing [29,43,44] followed by determining MLST type using *C. trachomatis* MLST database (mlstdb.bmc.uu.se).

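### Failure risk is divided by all women, but a same-strain positive after detected unprotected exposure is never counted as failure, so the estimate is biased downward

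*Protocol article*

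**What the plan says.** - **Target (Research aim).** "The primary aim is to estimate the proportion of women infected with chlamydia who fail treatment with 1 gram azithromycin".
- **Estimator (Statistical analysis).** "The population risk of treatment failure will be estimated as the observed proportion of women in the sample with treatment failure". The method for the interval is fixed in the same sentence: "with 95% CI calculated assuming an underlying binomial distribution". The denominator is not restricted by sexual exposure.
- **Failure rule (Primary outcome).** "Detection of same MLST type without detection of Y chromosome DNA or any reports of unprotected sex will be classified as treatment failure".
- **Re-infection rule (Primary outcome).** A different serovar is a re-infection. So is a repeat positive when the woman's "repeat specimen has the same MLST type and Y chromosome is detected or she reports unprotected sexual contact".
- **Precision (Sample size estimates).** "To detect a treatment failure risk of 8% with a 95% CI of 5.5%, 10.5%, 450 women are required". No source is cited there for the 8%.
- **Earlier figures near 8% (Background).** One comes from a trial of partner treatment and concerns women "who reported no sexual intercourse after treatment, 22 of 289 (8%; 95% CI: 5%, 11%) had persistent infection". The other is 7.9% in a cohort of adolescent females, with no denominator shown.
- **Timing (Partner notification; Primary outcome).** Women are advised to avoid sexual contact for 7 days. Test-of-cure specimens are taken at days 28, 42 and 56.

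**The concern.** The classification rule and the estimator do not fit together. A woman with Y chromosome DNA or reported unprotected sex cannot have a same-strain positive counted as failure, even if her first infection never cleared. She nevertheless stays in the denominator, and the quotient is presented as the population risk.

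Exposure before test of cure is foreseeable, because the advised abstinence ends three weeks before the first test. Partner treatment is recorded, but the stated rule does not use it: unprotected sex with a treated partner also turns a persistent infection into a re-infection.

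The Discussion contrasts about 8% with 2–3% and attaches opposite policy conclusions to failure and re-infection. The bias lowers the first and raises the second. Failures mislabelled in this way also enter the re-infection group of the multinomial model and blur the planned comparison of risk factors.

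**Working it through.** **1. The plan's own figure.** Inputs from Sample size estimates: risk 0.08, half-width 0.025, 95% confidence.

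n = 1.96² × 0.08 × 0.92 / 0.025² = 452.4, so 453 against the stated 450. At n = 450 the Wald interval for 8% is 5.49% to 10.51%. For 3% at n = 450, the Wilson interval is 1.78% to 5.02% and the Agresti–Coull interval 1.73% to 5.06%, in line with the stated 1.7% to 5.0%. The arithmetic is sound.

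**2. Expected value under the rule.** Let p be the true risk of persistent infection and e the share of women with detected unprotected exposure by the time of the positive test. If persistence is independent of exposure and all exposure is detected, only the unexposed share can supply failures:

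E[estimate] = p(1 − e), a relative bias of −e.

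The documents do not give e, so the values below are assumptions. Coverage is the probability that the exact 95% binomial interval at n = 450 contains 8% when the count is binomial with probability 0.08(1 − e).

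| e (assumed) | Expected estimate, true p = 8% | Coverage of 8% |
|---|---|---|
| 0 | 8.0% | 96% |
| 0.2 | 0.08 × 0.8 = 6.4% | 79% |
| 0.3 | 0.08 × 0.7 = 5.6% | 55% |
| 0.5 | 0.08 × 0.5 = 4.0% | 6% |

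**3. The opposing error.** Now let e be the share truly exposed, s the share of exposed women who are detected, and r the same-strain re-infection risk in exposed women. Undetected exposed women can be called failures whether they persisted or were re-infected:

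E[estimate] = p(1 − e) + e(1 − s)[p + (1 − p)r]

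- e = 0.5, s = 0.9, r = 0.10: 0.040 + 0.05 × (0.08 + 0.092) = 4.9%.
- e = 0.5, s = 0.8, r = 0.15: 0.040 + 0.10 × (0.08 + 0.138) = 6.2%.

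The two errors cancel when r = ps / [(1 − p)(1 − s)]. At s = 0.8 that is 0.064 / 0.184 = 0.35. At s = 0.9 it is 0.072 / 0.092 = 0.78. Below those values the net bias stays downward.

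**4. Precision among women without detected exposure.** With n = 450(1 − e) and p = 8%, the Wald half-width is 1.96 × √(0.08 × 0.92 / n):

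| e (assumed) | Unexposed women | Half-width |
|---|---|---|
| 0.2 | 360 | 2.8 points |
| 0.5 | 225 | 3.5 points |

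**5. Scale of the 8%.** 22/289 = 7.6%, and all 289 women reported no intercourse. That denominator corresponds to the unexposed women in this cohort, not to all women in the sample.

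**The case against.** The strongest reply is that a strict failure definition is a deliberate, conservative choice. Re-infection stays a separate outcome level, same-serovar repeats are sequenced in any case, and an upper figure could be computed from planned data. Bounds and sensitivity analyses are often left to a statistical analysis plan. This is fair for the definition and for supporting analyses. It does not reach the primary estimator, which the article fixes and names as the population risk. Figure 1 was not available for this check, but the Primary outcome section states the rule in words.

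Some of the reply limits the point:

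- **Only unprotected exposure matters.** A reader might infer that any sex after treatment removes a woman from the numerator. The rule does not say so: with condom-protected sex only and no Y chromosome DNA, she can still be a failure.
- **The size is not known.** A reader might infer that a true 8% would be reported as about 3%. That would need more than half of the women to be exposed by the positive test, and the documents give no such figure.
- **Undetected exposure works the other way,** as step 3 shows, so the net bias is smaller than e.
- **The origin of the planning 8% is not stated.** A reader might infer that it was taken from the 22/289 study. The Background gives two figures near 8%, and the algorithm is said to follow the method of the study reporting 7.9%, whose denominator is not shown and may match the planned one.
- **Day-0 specimens.** Because "Chlamydial fingerprinting will be conducted on specimens that are PCR positive at baseline and at test of cure", a reader might infer that women without a typed baseline specimen deepen the bias. Entry requires a positive test, no frequency is given, and the algorithm figure may cover the case.

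**Conclusion.** The point holds. As written, the estimator measures failure identified in the absence of detected unprotected exposure, per woman in the sample. This is below the risk named in the Research aim whenever exposed women can have persistent infection, unless missed exposure with same-strain re-infection is common enough to offset it.

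Under independence and full detection the relative bias equals the exposed share. For a true 8%, the expected estimate falls to between 6.4% and 4.0% as e goes from 0.2 to 0.5, and coverage falls from 79% to 6%. With imperfect detection the loss is smaller: at e = 0.5 the two cases tried gave 4.9% and 6.2%. These sizes rest on assumed values of e, s and r. The direction rests on the rule and the denominator, together with r staying below the break-even values in step 3.

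The sample size calculation is not in error. Its 5.5% to 10.5% interval describes the all-women proportion, not the risk among women in whom failure can be recognised. At least one of the two earlier figures near 8% is on the latter scale.

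**What to change.** Keep the classification rule and change what is reported.

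1. **Statistical analysis: relabel and bracket.** Present the all-women proportion as a conservative (lower) figure rather than the population risk. Report beside it the proportion that counts every same-MLST repeat positive as failure, as the upper figure. Say that the pair takes the strain typing as correct and that missed exposure can raise the lower figure.
2. **Statistical analysis: add an estimate in women without detected unprotected exposure.** At days 28, 42 and 56, take as the risk set the women still in follow-up with no Y chromosome DNA and no reported unprotected sex to that day. Combine the three by a life-table, censoring at first exposure. Do not simply restrict to women unexposed to day 56: a woman who fails early leaves follow-up and has less time to become exposed, so that restriction over-represents failures. State the assumption that exposure is unrelated to failure given measured covariates. It cannot be tested, because failure in exposed women is not identified; baseline comparisons can only make it more or less plausible.
3. **Sample size estimates.** State that 5.5% to 10.5% applies to the all-women proportion, and give the approximate half-width for the unexposed set: 2.8 points at e = 0.2 and 3.5 points at e = 0.5.

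The cost is a wider interval and one added assumption. The weekly swabs and questionnaires already supply the data, and no extra enrolment is asked for. Holding ±2.5 points in the unexposed set would instead need 453/(1 − e) evaluable women: about 566 at e = 0.2 and 906 at e = 0.5. Stating the wider interval is the practical course.
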